**Methods/design:**

In this pragmatic randomized controlled trial, 140 patients with unresectable (BCLC intermediate stage) hepatocellular carcinoma, with Eastern Cooperative Oncology Group performance status 0 to 1 and Child-Pugh A to B will be randomly assigned to either ^90^Y-RE or TACE with drug eluting beads. Patients assigned to ^90^Y-RE will first receive a diagnostic angiography, followed by the actual transarterial treatment, which can be divided into two sessions in case of bilobar disease. Patients assigned to TACE will receive a maximum of three consecutive transarterial treatment sessions. Patients will undergo structural follow-up for a timeframe of two years post treatment. Post procedural magnetic resonance imaging (MRI) will be performed at one and three months post trial entry and at three-monthly intervals thereafter for two years to assess tumor response. Primary outcome will be time to progression. Secondary outcomes will be overall survival, tumor response according to the modified RECIST criteria, toxicities/adverse events, treatment related effect on total liver function, quality of life, treatment-related costs and cost-effectiveness.

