### Study design

This is a pragmatic, multicenter, randomized controlled trial. Patients will be recruited after referral by their hepatologist or another treating physician. Treatment allocation will be performed by minimization, which is a valid alternative to standard randomization to ensure balance between groups for several prognostic factors [30]. The following prognosis-related patient characteristics will be taken into account: Child-Pugh stage (A/B), ECOG performance status (0/1), prior curative (resection or percutaneous ablation) treatment (yes/no) and bilobar disease (yes/no). The minimization procedure will be stratified by treatment center, with the aid of validated software, whereby a random component (10%) is to be introduced.

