#### ^90^Y-RE

^90^Y-RE will be performed using glass Yttrium-90 microspheres (TheraSphere®, MDS Nordion, Ottawa, Ontario, Canada). The target dose to the liver will be 100 to 120 Gy. The procedure will be carried out over two separate sessions: a work-up session and a treatment session. Meticulous work-up is very important because it determines the overall safety of the treatment. First, a selective visceral catheterization will be performed in order to obtain an angiographic map of the patients’ vascular anatomy. Branches feeding gastro-intestinal organs arising from the hepatic arteries must be identified. Radioactive microspheres, administered into the hepatic artery, should be prevented from ending up in extrahepatic organs via this route. The interventional radiologist will actively look for the presence of the gastroduodenal artery, right gastric artery, cystic artery and pancreaticoduodenal branches. If required, these arteries will be embolized using coils, taking the planned catheter position for injecting the microspheres into account. Additionally, 150 MBq Technetium-99 m-labeled macro aggregated albumin (^99m^Tc-MAA) will be injected. ^99m^Tc-MAA is used as a surrogate in order to predict the distribution pattern of ^90^Y-microspheres [31]. The distribution of ^99m^Tc-MAA will be visualized by whole body planar imaging and single-photon emission computed tomography (SPECT-CT), including low dose computer tomography of the abdomen. Accordingly, lung shunt fraction can be calculated and deposition of ^99m^Tc-MAA in the abdominal organs, such as the stomach, duodenum and pancreas, can indicate patent extrahepatic vessels distal to the injection site. In case a lung dose exceeding 30 Gy (610 MBq) in a single treatment (or 50 Gy cumulatively in case of repeated treatment) is predicted, an activity reduction will be prescribed [32].

In case a patient has an unfavorable ^99m^Tc scintigraphy, the ^99m^Tc-MAA workup procedure will be repeated, if feasible, to detect the cause of the extrahepatic deposition (for example, previously undetected patent extrahepatic vessels arising from the hepatic artery) and a solution will be searched for (for example, more selective placement of the catheter during injection). In the unlikely event no solution can be found and ^90^Y-RE cannot be performed, the patient will be treated according to best medical practice and will still enter the intention-to-treat analysis in the ^90^Y-RE arm.

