When the ^99m^Tc-MAA scintigraphy has a favorable outcome, patients will be readmitted to the hospital for the treatment session within two weeks. The volume of liver lobe to be treated and corresponding liver mass will be determined using CT or MRI. The activity is chosen to deliver an absorbed dose of about 120 Gy to the treatment zone in patients with no manifest risk factors for subsequent liver decomposition. If a patient presents at inclusion with elevated bilirubin or Child-Pugh B status, the activity will be reduced in order to reach an absorbed dose of 80 to −100 Gy in the target volume, but in the case of selective treatment on a segmental level a dose up to 150 Gy may be administered. The radioactivity required to deliver the desired dose to the liver will be calculated using the following formula:

$$\text{Activity Required}\;\left(\text{GBq}\right)=\frac{\left[\text{Desired}\;\text{Dose}\left(Gy\right)\right]\;\left[\text{Liver}\;\text{Mass}\left(kg\right)\right]}{50}$$

The actual liver dose (Gy) delivered to the liver after injection can be calculated using the following formula:

$$\text{Dose}\;\left(Gy\right)=\frac{50\;\left[\text{Injected}\;\text{Activity}\left(GBq\right)\right]\;\left[1-F\right]}{\text{Liver}\;\text{Mass}\left(kg\right)}$$

where F is the fraction of injected radioactivity localizing in the lungs, as measured by ^99m^Tc-MAA scintigraphy.

The hepatic artery will be catheterized and the ^90^Y-microspheres will be administered from the exact same microcatheter position as where the ^99m^Tc-MAA was administered. Injection of ^99m^Tc-MAA and ^90^Y therapy will be performed as selectively as possible. In case of bilobar disease, the right and left lobe will be treated in two separate sessions, with a generally accepted interval of 30 to 45 days. The moment of the first treatment will be regarded trial entry.

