### Follow-up

Patients will undergo structural follow-up for a timeframe of two years post treatment. Each patient will be seen by the treating physician during regular visits to the outpatient clinic, during which laboratory examination will also be performed (complete blood count, electrolytes, kidney function tests, liver function tests, albumin, Prothrombin time/INR, alpha-fetoprotein). Post-procedural, contrast-enhanced MRI will be performed one month after trial entry (the date of the first treatment T0), three months after trial entry and at three monthly intervals thereafter for two years to assess tumor response. MRI will be performed on 1.5-T scanners using a spoiled gradient-echo T1-weighted sequence and fast spin-echo T2-weighted sequence with fat suppression. A dynamic multiphase, contrast-enhanced, spoiled gradient-echo T1-weighted sequence with arterial, portal, equilibrium and delayed phase will be performed. In patients in which MRI is contra-indicated or who are not capable of breath holding, contrast enhanced CT will be carried out. Adverse events and toxicities will be recorded according to the National Cancer Institute Common Terminology Criteria for Adverse Events (CTCAE version 4.0). These criteria define adverse events on a scale from 1 to 5, corresponding to severity (grade 1: mild, grade 2: moderate, grade 3: severe, grade 4: life-threatening or disabling, grade 5: resulting in death). Toxicity will only be recorded if the grade increases from baseline. Adverse events and toxicities will be monitored for six months following the last treatment procedure. Patients will be asked to fill out questionnaires for quality of life assessment before treatment and at 1, 3, 6 and 12 months after first treatment. Quality of life will be measured with the EuroQol Group 5-Dimension Self-Report Questionnaire (EQ-5D), the cancer specific EORTC QLQ-C30 and its HCC specific supplement EORTC QLQ-HCC18 and an abbreviated version of the Short Form – Health and Labor Questionnaire (SF-HLQ).

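### The baseline quality-of-life questionnaire is tied to treatment rather than to minimization, so it may be completed after allocation and, in the 90Y-RE arm only, after an invasive work-up

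*Protocol article*

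**What the plan says.** The Follow-up section of the protocol article fixes the timing of the patient-reported outcomes. Patients complete "questionnaires for quality of life assessment before treatment and at 1, 3, 6 and 12 months after first treatment". The instruments are the EQ-5D, the EORTC QLQ-C30, its HCC18 supplement and a short form of the SF-HLQ. The same section times the first follow-up MRI at "one month after trial entry (the date of the first treatment T0", so first treatment starts the follow-up clock.

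Under Study design, "Treatment allocation will be performed by minimization". The Abstract (Methods/design) then gives the order of events in one arm: "Patients assigned to ^90^Y-RE will first receive a diagnostic angiography, followed by the actual transarterial treatment". The 90Y-RE section adds: "The procedure will be carried out over two separate sessions: a work-up session and a treatment session". The first of these is invasive: "First, a selective visceral catheterization will be performed in order to obtain an angiographic map of the patients’ vascular anatomy". It can also include coil embolization and an injection of labelled albumin, and it may be repeated if the scintigraphy is unfavorable. After a favorable result, "patients will be readmitted to the hospital for the treatment session within two weeks", and "The moment of the first treatment will be regarded trial entry".

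The TACE section describes no separate session before the first treatment. Under Assessment before treatment, the pre-procedural MRI must fall in the four weeks before minimization. Under Statistical analyses, quality of life is compared between arms over time with a linear mixed model. The role of the baseline score in that model is not stated.

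**The concern.** A baseline score is useful because allocation cannot have influenced it. That holds only if it is collected before allocation. Here the rule refers to treatment, and in the article's own vocabulary the treatment session of the 90Y-RE arm comes after the work-up session. A site that hands out the forms at readmission complies with the rule, yet the score then reflects knowledge of the allocated arm and recent catheterization. In the TACE arm the score could reflect knowledge of the arm, but no comparable procedure.

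At stake is the between-arm comparison of quality of life, a secondary outcome. If the baseline mean moves in one arm for reasons caused by allocation, a comparison that subtracts baseline, adjusts for it, or assumes equal baseline means takes on part or all of that movement. A lowered 90Y-RE baseline would make later scores look like improvement and would hide the burden of the work-up; a raised one would do the reverse. Baseline EQ-5D, if it enters the cost-effectiveness calculation, would carry the same distortion. No later analysis plan can repair this, because a pre-allocation score that was never collected cannot be recovered.

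**Working it through.** No figure in the article is in question, so there is none to reproduce. The check is one of sequence, followed by an illustration of sensitivity.

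**Order of events, from the sections cited above**

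| Step | 90Y-RE | TACE |
|---|---|---|
| Pre-procedural MRI | before minimization | before minimization |
| Minimization | yes | yes |
| Separate invasive work-up | yes, possibly repeated | none described |
| Interval to treatment session | up to two weeks after a favorable work-up | not applicable |
| First treatment (trial entry) | yes | yes |
| Latest baseline questionnaire that the rule allows | after minimization and work-up | after minimization |

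Two statements place the work-up after allocation. The Abstract says that patients already assigned to 90Y-RE receive it first. The 90Y-RE section keeps a patient whose work-up rules out treatment in that arm's intention-to-treat analysis.

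**Sensitivity (illustration only)**

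Inputs: n = 70 per arm (Sample size calculation); no true effect; SD of 1 at baseline and follow-up; one follow-up visit with complete data; normal approximation. Two inputs are assumptions with no source in the article: d, the mean baseline shift in the 90Y-RE arm relative to TACE, in SD units; and rho, the correlation between baseline and follow-up.

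- Change score: bias = d; standard error = sqrt(2(1 − rho)) × sqrt(2/70).
- Baseline as a covariate: bias = rho × d; standard error = sqrt(1 − rho²) × sqrt(2/70).
- With z = bias / standard error, the two-sided error rate = 1 − Φ(1.96 − z) + Φ(−1.96 − z).

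Worked case, rho = 0.5 and d = 0.2, with sqrt(2/70) = 0.169:

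- Change score: standard error = 1 × 0.169; z = 0.2/0.169 = 1.18; error rate 21.9%.
- Covariate: standard error = 0.866 × 0.169 = 0.146; z = 0.1/0.146 = 0.68; error rate 10.5%.

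| rho | d | Change score: bias, error rate | Covariate: bias, error rate |
|---|---|---|---|
| 0.5 | 0.1 | 0.10, 9.1% | 0.05, 6.3% |
| 0.5 | 0.2 | 0.20, 21.9% | 0.10, 10.5% |
| 0.5 | 0.3 | 0.30, 42.7% | 0.15, 17.6% |
| 0.5 | 0.5 | 0.50, 84.1% | 0.25, 40.1% |
| 0.7 | 0.1 | 0.10, 11.9% | 0.07, 8.9% |
| 0.7 | 0.2 | 0.20, 33.3% | 0.14, 21.3% |
| 0.7 | 0.3 | 0.30, 63.0% | 0.21, 41.3% |
| 0.7 | 0.5 | 0.50, 96.8% | 0.35, 82.6% |

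Here d is the mean shift across the whole arm. If only some patients complete the form late, d is correspondingly smaller. If the questionnaire precedes minimization, d = 0 in expectation, the bias is 0 and the error rate is 5%.

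**The case against.** The best defense is that a questionnaire completed before minimization also meets the rule. Nothing in the article says that the forms are given at readmission. A site could read treatment as the whole 90Y-RE procedure, work-up included, and the full protocol's visit schedule may be tighter. All of this stands: the text permits a late baseline but does not require one. It does not remove the point, because the article does state a timing rule and ties it to an event that follows allocation in both arms and the work-up in one. For the MRI, the same article ties the assessment to minimization.

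Three stronger readings are tempting, and the article supports none of them.

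- A reader might infer that the quality-of-life result will be biased. Whether late completion occurs, and how far and in which direction it would move scores, cannot be known from the article. That the trial is open is itself an inference, from visibly different procedures and the absence of any described blinding of patients.
- A reader might infer that change from baseline is the planned analysis. The article names only a linear mixed model over time. A comparison of post-treatment scores that makes no use of baseline would escape the problem.
- A reader might infer that an earlier baseline would bring patients who are never treated back into the intention-to-treat comparison. It would not, because the later questionnaires are timed from first treatment and these patients have no such date. A mixed model that treats baseline as one of the repeated outcomes would also not drop a patient merely for a missing baseline.

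Knowledge of the arm can also affect every follow-up score, whatever is done about the baseline.

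**Conclusion.** The point holds as a weakness in the timing rule. The rule allows a baseline that is post-allocation in both arms and post-work-up in one, and the resulting arm-specific shift could bias arm-by-time contrasts, baseline-adjusted comparisons and any baseline EQ-5D used in the cost-effectiveness analysis. Size and direction are unknown. The error rates above, 6% to 97% across the assumed shifts and correlations, show sensitivity and are not an estimate for this trial.

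The conclusion rests on three things: patients know their arm, the mixed model uses the baseline score in some form, and at least some sites collect the forms late. It concerns a secondary outcome and leaves the primary time-to-progression analysis untouched. It is a minor point, worth making because the remedy is almost free and the loss cannot be made good afterwards.

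**What to change.** In the Follow-up section, require the baseline questionnaires to be completed after written consent and before minimization in both arms, in line with the rule already set for the pre-procedural MRI. State that this score is the baseline in the linear mixed model. The follow-up times need not change.

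The cost is one sentence and an instruction to sites. No questionnaire is added, and probably no visit, since written consent is already a condition of inclusion. There is one small drawback: the Trial status section reports 10 patients already minimized and treated, 10/140 = 7% of the planned sample. Their baselines may have been taken under the looser rule. Record the questionnaire date relative to minimization and work-up, and flag those patients so that two baseline definitions are not pooled unnoticed.

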### Objective

The objective of this study is to compare the efficacy and safety of TACE versus ^90^Y-RE in patients with intermediate stage HCC.

### Outcomes

#### Primary outcome

The primary outcome will be Time to Progression (TTP), defined as the time elapsed since the start of treatment until the determination of progressive disease. Progressive disease will be determined by image evaluation according to the modified RECIST (mRECIST) response evaluation criteria [33]. The mRECIST overall response assessment includes the evaluation of target lesions response, non-target lesions response and the occurrence of new lesions.

The baseline for calculation of TTP will be the date of minimization. Imaging data will be assessed by independent radiologists. In case progressive disease is determined during follow-up, patients have reached the study endpoint and will be treated according to best medical practice. Patients who switch to other treatments are registered as such and overall survival will be monitored.

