#### Secondary outcomes

1: Time to Local Progression (TLP). ‘Target liver volume’ will be determined with the use of cone-beam CT during the interventional procedure, by implementing the perfusion area of the targeted vessel in relationship to the anatomic localization of the liver lesion(s). TLP will be defined as the time elapsed since the start of treatment (baseline is the date of minimization) until *local* tumor progression, ‘local’ indicating a constriction to the target liver volume as defined by cone-beam CT. Local tumor progression will be based on the mRECIST criteria and defined as: An increase of at least 20% in the sum of the diameters of viable (enhancing) target lesions (whereas target lesions for TLP evaluation are only considered within the ‘target liver volume’), taking as a reference the smallest sum of the diameters of viable (enhancing) target lesions recorded since treatment started, and/or unequivocal progression of existing no target lesions within this perfusion area and/or the appearance of one or more new (enhancing) lesions within this perfusion area; 2: Overall survival; 3: Overall response to therapy according to mRECIST; 4: Toxicities and adverse events; 5: Quality of life; 6: Treatment-related costs, in terms of cost of therapy and number of hospitalization days, in these patients. Cost-effectiveness of ^90^Y-RE versus TACE will be assessed.

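### TTP and TLP each have two start dates while every MRI is timed from first treatment; if first treatment comes later after radioembolization allocation, as is likely, the primary comparison is biased

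*Protocol article*

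**What the plan says.** Under Primary outcome, TTP is "defined as the time elapsed since the start of treatment until the determination of progressive disease". The next paragraph of that section says "The baseline for calculation of TTP will be the date of minimization". Under Secondary outcomes, TLP joins both origins in one sentence: "the time elapsed since the start of treatment (baseline is the date of minimization".

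The imaging calendar follows the treatment date. Under Follow-up, "MRI will be performed one month after trial entry (the date of the first treatment T0), three months after trial entry", and then "at three monthly intervals thereafter for two years to assess tumor response". The TACE and radioembolization sections both define trial entry as the first treatment.

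The two arms reach that date differently. The radioembolization section sets out a work-up session and a separate treatment session. If work-up is favourable, "patients will be readmitted to the hospital for the treatment session within two weeks"; if it is unfavourable, work-up is repeated where feasible. Work-up follows allocation, because a patient who cannot go on to radioembolization "will still enter the intention-to-treat analysis" in that arm. The TACE section describes no comparable step. Neither section gives the time from minimization to first treatment.

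**The concern.** Minimization and first treatment are different dates, so the primary endpoint has two incompatible origins, and two analysts could derive different TTP values from the same data.

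The choice matters because progression is only found at scans. If the clock starts at minimization and the scans at treatment, an arm that waits longer for treatment has all its scans shifted later on the TTP clock. The log-rank test then compares arms with staggered detection times, and part of any difference may reflect scheduling rather than treatment.

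If the clock starts at treatment, that stagger disappears, but a patient who fails work-up may have no first treatment date. That patient would have neither a TTP origin nor a scan calendar, yet stays in the intention-to-treat analysis.

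**Working it through.** The plan gives no figure of its own for this point, so there is none to reproduce.

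**Inputs from the protocol article.** 70 patients per arm; median TTP 13.3 months; 24 months of follow-up; target difference 20%, or 2.7 months (0.20 × 13.3 = 2.66); log-rank test at two-sided 5%; MRI at 1 and 3 months, then three-monthly to 24 months after first treatment; work-up to radioembolization within two weeks, about 0.5 month.

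**Assumptions, not in the documents.** The wait from minimization to treatment in each arm, the spread of visits around their planned dates, exponential TTP, and a progression risk that runs from minimization.

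**Mechanism.** Take waits of 0.25 month (TACE) and 0.75 month (radioembolization). The three-month scans then fall at 3.25 and 3.75 months on the minimization clock. The chance of progression in a three-month interval is 1 − 2^(−3/13.3) = 0.145, so about 10 of 70 progress in each arm. At the TACE scan the log-rank test expects 10 × 70/140 = 5.00 radioembolization events. At the radioembolization scan only 60 TACE patients remain at risk, and it expects 10 × 70/130 = 5.38. The total expected is 10.38 against 10 observed, so radioembolization looks better although nothing differs. This recurs at each scan. After the last TACE scan no TACE patient is left at risk, so the progressions found at the last radioembolization scan carry no weight. The bias comes from the order of detection and need not show in the medians: with a 0.5-month extra wait and visits within ±0.25 month, the simulated medians were 14.9 (radioembolization) and 15.1 months (TACE).

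**Simulation under no true effect, clock at minimization, scans from first treatment.** Mean wait 0.25 month for TACE, individual waits 0.5 to 1.5 times the arm mean, 2,500 trials per row. HR is radioembolization versus TACE.

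| Extra wait (months) | Visit spread (months) | HR | Two-sided type I error |
|---|---|---|---|
| 0 | ±0.1 to ±0.5 | 1.00 | 4.5-4.6% |
| 0.25 | ±0.1 / ±0.25 / ±0.5 | 0.88 / 0.91 / 0.94 | 9.4 / 6.5 / 5.8% |
| 0.5 | ±0.1 / ±0.25 / ±0.5 | 0.88 / 0.89 / 0.92 | 10.3 / 8.3 / 6.7% |
| 1.0 | ±0.1 / ±0.25 / ±0.5 | 0.91 / 0.91 / 0.92 | 7.7 / 8.0 / 7.2% |

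The Monte Carlo standard error near 5% is √(0.05 × 0.95/2,500) = 0.4 percentage points. At 0.5 month, 5.6-9.6% of trials falsely favour radioembolization and 0.7-1.1% falsely favour TACE.

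**More variable waits.** With a common wait of 0 to 1.5 months in both arms, an extra 0 to 0.5 month and visits within ±0.25 to ±0.5 month, HR is 0.96-0.97 and the error 4.7-5.0%.

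**Clock and scans both from first treatment.** HR 1.03 and 5.6% at an extra 0.5 month; HR 1.08 and 6.6% at 1.0 month. The direction reverses because time at risk before treatment is cut off, and more is cut off in the arm that waits longer.

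**Clock and scans both from minimization.** HR 1.00, with error 4.7% and 4.6% at extra waits of 0.5 and 1.0 month.

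**Clock at minimization, scans from treatment, interval-censored proportional hazards model.** HR 0.99-1.01.

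**Scale.** A 20% difference corresponds to HR 10.64/13.3 = 0.80. On the log scale, ln 0.88/ln 0.80 = 0.57 and ln 0.97/ln 0.80 = 0.14, so the null bias is between about one seventh and somewhat over half of the planned effect.

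**A case outside the range.** If progression risk began only at first treatment, the minimization clock would give HR 0.84-0.85 and 12.6-14.0% error at extra waits of 0.5 and 1.0 month, and the treatment clock 1.00. An untreated tumour is unlikely to behave this way, so I do not use these figures.

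**The case against.** The strongest reply is that the arm difference in waiting time is nowhere stated. That TACE patients go to treatment without delay is read from the silence of the TACE section, and their waiting time is unknown. This stands: a later average first treatment after radioembolization allocation is well supported by the work-up step, but it is not a documented fact, and not every radioembolization scan need fall later.

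Second, the size is fragile. The largest bias appears when visits fall almost exactly on schedule, so that the two arms' scans barely overlap on the clock. A longer assumed wait does not always give more bias, and visit spread or variable waits shrink it, in some settings to almost nothing. This also stands, and is why only a range can be given.

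Third, the text leans towards minimization: the sentence on the baseline is the operational rule, and the TLP definition repeats it in brackets. Under that reading patients who fail work-up keep a start date, and the article calls such failures unlikely. That is fair, but it does not remove the contradictory wording, and the minimization reading is the one under which treatment-timed scans favour radioembolization. Scan arrangements for patients never treated as allocated may be in the full protocol, so I make no separate point of them.

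A reader might infer that the endpoint is shown to be biased towards radioembolization, with HR near 0.89 and a 9-10% false-positive rate. The documents do not support that. Those figures belong to the upper part of the range, need an assumed wait, and apply only to the minimization clock.

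**Conclusion.** The point holds as a contradiction with a conditional consequence. That TTP and TLP each have two origins, with scans tied to first treatment, is plain from the text and needs no assumption (high confidence).

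The bias depends on an extra radioembolization wait that the documents imply but do not quantify. For an assumed 0.25 to 1 month, the minimization clock with treatment-timed scans gives a null HR of about 0.88-0.97 and a two-sided type I error of about 5-10%, with the excess favouring radioembolization. The treatment-start clock gives a smaller bias that can reverse (about 1.03-1.08) and may leave some intention-to-treat patients without an origin. Confidence in the size is moderate.

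This should be fixed. Since the choice of origin can change even the direction of the bias, it should be settled before outcome data are examined.

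**What to change.** Delete the references to the start of treatment from the TTP and TLP definitions. Measure both from the date of minimization for all randomized patients, including those never given the allocated treatment.

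Keep the log-rank test as the primary test. Pre-specify an interval-censored proportional hazards analysis, with progression lying between the last progression-free scan and the first scan showing progression, and report the minimization-to-treatment interval by arm. The scans would still differ in timing; the model accounts for this. It does not remove any real effect of waiting longer for treatment, which is part of a comparison from allocation. The cost is one extra analysis and a short text change.

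Alternatively, time the progression scans from minimization in both arms. This also removed the bias in simulation, but it is more than a wording change. The three-month MRI informs the decision on a third TACE session, so the TACE and Follow-up sections would have to be reconciled, and radioembolization patients would probably be scanned somewhat sooner after treatment. The cost is a small calendar amendment, at a point where the article reports only the first 10 patients treated.
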